### 9.6. Follow-up

After the initial AE/SAE report, the Investigator is required to proactively follow each subject and provide further information to the Sponsor (or its designee) on the subject’s condition. All AEs and SAEs documented as ongoing will be followed and reviewed until they resolve, they become medically stable in the Investigator’s opinion, or 4 weeks have passed after the last visit, whichever occurs first.

### 9.7. Relationship or Causality

The Investigator will use clinical judgment to assess AEs for relationship to the study drug, and will also consult the Investigator’s Brochure for the study drug and/or the product or prescribing information for the concomitant medications that are marketed products in making his/her assessment.

The assessments will be recorded on the source documents and eCRF, using the categories defined below:

- Unlikely:** A clinical event, including laboratory test abnormality, with a temporal relationship to drug administration which makes a causal relationship improbable, and in which other drugs, chemicals, or underlying disease provide plausible

explanations. For the purpose of this protocol, the term “unlikely” will be considered an AE not related to study drug.

**Possible:** A clinical event, including laboratory test abnormality, with a reasonable time sequence to administration of the drug, but which could also be explained by concurrent disease or other drugs or chemicals. Information on drug withdrawal may be lacking or unclear.

**Probable:** A clinical event, including laboratory test abnormality, with a reasonable time sequence to administration of the drug, unlikely to be attributed to concurrent disease or other drugs or chemicals, and which follows a clinically reasonable response on withdrawal.

If the relationship between the AE/SAE and the study drug is determined to be “possible” or “probable” the event will be considered to be related to the study drug for the purposes of expedited regulatory reporting.

### 9.8. Reporting Adverse Events

All SAEs, whether or not unexpected or considered to be associated with the use of the drug, and regardless of the timing of their occurrence after the first dose of study drug, will be reported to the Sponsor’s Medical Monitor or designee by the Investigator through telephone, fax, or email within 24 hours of discovery, using the form provided by the Sponsor. The Medical Monitor or designee will then notify the Sponsor and advise the Investigator regarding the nature of any further information or documentation that is required. Contact information for SAE reporting is provided in Table 9-1.

Any SAE occurring in a subject after the EOS or ET assessments that comes to the attention of the Investigator and is considered to be causally related to the study drug will also be communicated to the Sponsor, following the same instructions as for SAEs occurring during the study. The Investigator must inform the IRB immediately regarding any AE (does not have to be causally related) that is both serious and unexpected; or that represents a series of AEs that, on analysis, is unanticipated, or occurs at an unanticipated frequency, or otherwise represents an unanticipated safety risk to the study subject. The IRB may subsequently choose to modify the informed consent or request changes to the protocol.

All SAEs must be followed with appropriate medical management until resolved or until considered chronic and stable or otherwise explained.

All paper documents relating to the SAE (e.g., the original SAE form and fax transmission confirmation, copies of any supporting documentation, all SAE-related correspondence with the IRB) will be retained in the site's study file. Copies of all documents will be forwarded to the Study Monitor.

## **9.9. Stopping Rules**

The Investigator or medically-qualified designee must contact the Sponsor immediately to discuss whether to suspend dosing if he/she believes AEs and/or laboratory abnormalities indicate that continued dosing of subsequent subjects would not be tolerated or would jeopardize the subjects' safety. The Sponsor may suspend dosing at any time for any reason.

Factors that must be considered for suspension of dosing include the frequency, severity, CS, possible causality, and anticipated reversibility of all observed AEs and/or laboratory abnormalities for each specific subject group. If any CS, treatment-related SAE is observed in at least 1 subject, dosing of subsequent subjects will be stopped pending a safety review of the data and a consideration of the appropriate course of action by Sponsor and Investigator. The IRB will be notified if dosing is suspended.

The study will be immediately suspended and no additional doses of study drug will be administered if one or more subjects develop any of the following SAEs deemed to be possibly or probably attributable to study drug by the Investigator and/or Sponsor Medical Monitor, based upon close temporal relationship or other factors:

- Death
- Serious anaphylaxis characterized by severe angioedema, hypotension, shock, bronchospasm, hypoxia, or respiratory distress

- Seizure in any subject
- QTcF  $\geq 500$  msec and confirmed on repeat ECG
- 1 subject with serum alanine aminotransferase (ALT) or aspartate aminotransferase (AST)  $> 5x$  above upper limit of normal (ULN), or serum total bilirubin  $> 2x$  ULN, or serum creatinine  $> 2x$  ULN
- 2 subjects with  $> 3x$  ULN ALT or AST, or serum total bilirubin  $> 1.5x$  ULN, or serum creatinine  $> 1.5x$  ULN

In addition, dose hold or discontinuation of IV GTX-104 dosing for any subject may occur if changes in BP and/or heart rate are noted, as described in [Appendix 2](#).

Vital signs can be repeated, as appropriate, to confirm values and rule out extraneous results. Determination of early termination will be made based on clinical findings at the Investigator's discretion. If the IV infusion is stopped due to the above-referenced hemodynamic criteria, then the subject will be discontinued from the study.

The BP and heart rate criteria in Appendix 2 will be used once dosing has commenced. The vital signs outlined in the Inclusion/Exclusion Criteria (Section 5.1, Section 5.2) will be used for Screening and baseline evaluations only.

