| Prior medication assessment                                          | X                      | X               |                                    |                                                       |                                                  |                                                        |
| Full physical examination                                            | X                      |                 |                                    |                                                       |                                                  |                                                        |
| Brief physical examination                                           |                        | X               |                                    |                                                       |                                                  | X                                                      |
| Height measurement                                                   | X                      |                 |                                    |                                                       |                                                  |                                                        |
| Weight measurement                                                   | X                      | X               |                                    |                                                       |                                                  | X                                                      |
| Body mass index                                                      | X                      |                 |                                    |                                                       |                                                  |                                                        |
| 12-lead electrocardiogram                                            | X                      |                 |                                    |                                                       |                                                  | X                                                      |

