### **9.1.3. Serious Adverse Event**

An AE is considered “serious” (that is, an SAE) if, in the view of either the Investigator or Sponsor, it results in any of the following outcomes:

- Death.
- A life-threatening AE (at risk of death at the time of the event).
- Inpatient hospitalization or prolongation of existing hospitalization.
- A persistent or significant disability/incapacity or substantial disruption of the ability to conduct normal life functions.
- A congenital anomaly/birth defect.

Important medical events that may not result in death, be life-threatening, or require hospitalization may be considered serious when, based upon appropriate medical judgment, they may jeopardize the subject and may require medical or surgical intervention to prevent one of the outcomes listed in the SAE definition.

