### 9.4. Clinical Laboratory Adverse Events

The Investigator will exercise medical judgment in deciding whether abnormal laboratory values, ECGs, or other assessment are CS.

Abnormal laboratory findings (e.g., clinical chemistry, hematology, coagulation, urinalysis) or other abnormal assessments (e.g., ECGs, vital signs) that are judged by the Investigator as CS will be recorded as AEs or SAEs if they meet the definition of an AE or SAE (as defined in Section 9.1).

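### Section 9.9 limits automatic suspension to SAEs, yet three of its six triggers are QTcF or laboratory values that are not SAEs by themselves

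*Protocol*

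**What the plan says.** Section 9.9 has three layers.

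- **Discretionary.** The opening paragraph obliges the Investigator to contact the Sponsor at once if he or she believes that AEs or laboratory abnormalities make further dosing unsafe. The Sponsor may suspend at any time.
- **Any related SAE.** The next paragraph states: "If any CS, treatment-related SAE is observed in at least 1 subject, dosing of subsequent subjects will be stopped pending a safety review".
- **Automatic list.** This layer halts the whole study, so that "no additional doses of study drug will be administered". The condition for the halt reads: "if one or more subjects develop any of the following SAEs deemed to be possibly or probably attributable to study drug". Six entries follow: death, serious anaphylaxis, seizure, QTcF of at least 500 "msec and confirmed on repeat ECG", a laboratory rule for one subject and a laboratory rule for two subjects. The two-subject rule begins at more than 3 times "ULN ALT or AST, or serum total bilirubin" and continues with lower bilirubin and creatinine limits than the one-subject rule.

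Section 9.1.3 defines an SAE by five outcomes. It adds that important medical events outside those outcomes "may be considered serious when, based upon appropriate medical judgment", they put the subject at risk or may need intervention.

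Section 9.4 says that clinically significant laboratory and ECG findings "will be recorded as AEs or SAEs if they meet the definition of an AE or SAE". Sections 8.7 and 8.9 send a clinically significant ECG or laboratory result to the AE record and do not mention SAEs.

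In Table 4-1 the row "12-lead electrocardiogram" is marked at Screening and EOS/ET only. The clinical laboratory row is marked at Screening, Admission and EOS/ET.

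**The concern.** A list of automatic triggers is useful because it leaves no room for debate on the day. Here the lead-in asks that the event be an SAE, while half the entries are numeric findings that become SAEs only through a case-by-case judgement. The same result can therefore be handled in two ways. Site staff who follow the words would record an asymptomatic, related ALT above 5 times ULN, or a confirmed QTcF of 500 msec, as an AE and would not invoke the list. Staff who follow the evident intent would suspend the study.

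What is at stake is the automatic stop for these findings. For a completer, the scheduled post-dose ECG and chemistry come after that subject's own dosing. On scheduled tests, then, the limits serve mainly to protect other subjects, and that is where the SAE condition can block them.

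**Working it through.** The plan states no figure to reproduce. The check is a count and a side-by-side reading.

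**1. Count the numeric entries (Section 9.9).**

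| Entry | Limits | Printed thresholds | ALT and AST counted separately |
|---|---|---|---|
| Death, anaphylaxis, seizure | none | 0 | 0 |
| QTcF | at least 500 msec, confirmed | 1 | 1 |
| One subject | ALT or AST >5x, bilirubin >2x, creatinine >2x ULN | 3 | 4 |
| Two subjects | ALT or AST >3x, bilirubin >1.5x, creatinine >1.5x ULN | 3 | 4 |
| Total | 3 of 6 entries are numeric | 1 + 3 + 3 = 7 | 1 + 4 + 4 = 9 |

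**2. Compare with the SAE definition (Section 9.1.3).** The five outcomes are death, a life-threatening event, hospitalization, disability and congenital anomaly. None of the seven thresholds (or nine limits) is among them. The remaining route is the important-medical-event clause, which is permissive.

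**3. Follow the default record.** Section 8.7 makes a clinically significant post-admission ECG an AE. Section 8.9 does the same for laboratory results. Section 9.4 raises either to an SAE only if the definition is met. So the protocol's default for these findings is AE, while the list asks for SAE.

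**4. Apply the list literally to one case.** Take a related, asymptomatic ALT of more than 5 times ULN, judged clinically significant but not serious.
- Automatic list: the attribution condition is met, the SAE condition is not, so there is no automatic suspension.
- Related-SAE paragraph: not met, for the same reason.
- Opening paragraph: applies if the Investigator believes continued dosing is unsafe. Contact is then mandatory and suspension is a decision.

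**5. Test the two-subject rule.** If its values count only as SAEs, the first related, clinically significant one already stops dosing of subsequent subjects. The second can add only the halt to subjects already being dosed. The step from higher limits in one subject to lower limits in two makes sense only if the values are triggers in their own right. An SAE is also an event in one subject, so an entry that needs two subjects cannot itself be an SAE.

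**6. Check when scheduled tests can meet the limits.** After first dose, both the ECG and the laboratory rows of Table 4-1 are marked only in the EOS/ET column. The three chemistry samples in Appendix 1 agree (Screening, Admission, EOS/ET). Section 4.3.4 puts EOS after the final PK sample. A completer has therefore finished dosing before the first scheduled result that could meet a limit.

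**The case against.** The best defence is that the lead-in can be read as naming what the Sponsor treats as serious for this rule. Section 9.1.3 leaves seriousness to the view of the Investigator or the Sponsor and allows for important medical events, so the list could be that judgement made in advance. The intent is plain, and many readers would act on it. But the text does not say that the listed values are deemed serious, Sections 8.7, 8.9 and 9.4 point the other way, and the two-subject entry does not fit the reading. An immediate-suspension rule should not depend on a reader choosing the sensible interpretation.

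A second defence is that abnormal values are covered elsewhere in 9.9. This stands in part. A reader might infer that a non-serious value has no route to suspension. That is not so: the opening paragraph makes contact with the Sponsor mandatory once the Investigator has the concern, with no requirement that the event be serious. What is lost is automatic action.

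The mismatch between the lead-in's count and the two-subject entry is minor, since each laboratory entry states its own number.

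Three further inferences are tempting and are not supported.
- *The test schedule is at fault.* Section 3.3 sets the laboratory and ECG endpoints at the end of the study, and the sparse schedule is a deliberate choice for healthy subjects.
- *The limits can be met only at EOS.* Subjects who stop early have the same tests at ET, and unscheduled tests can meet the limits at any time, under the same wording.
- *An EOS result cannot trigger the rule because it cannot be assigned to one product.* Section 4.3.3.1 gives an attribution rule by dosing period, and the trigger does not require a choice between two nimodipine products.

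**Conclusion.** The point holds as a wording defect in a safety rule. Three of six automatic triggers, carrying seven printed thresholds, sit under an SAE condition that they do not meet by themselves. Read literally, a related value beyond these limits that is not judged serious triggers no automatic suspension, and the discretionary route alone applies. The two-subject rule is close to redundant on the same reading.

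The conclusion rests on the text of Sections 8.7, 8.9, 9.1.3, 9.4 and 9.9 and assumes that site staff follow the lead-in as written. It does not depend on how many doses are given before a result arrives: that follows from a schedule that is not in dispute and that the fix leaves alone. The trial's estimates, power and error rates are unaffected. The correction is worth making but minor.

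**What to change.** Change the lead-in of the Section 9.9 list only. In place of the clause that restricts the list to SAEs in at least one subject, write: *if any of the following events occurs, in the number of subjects stated (one unless given), whether or not it meets the SAE definition in Section 9.1.3*. Keep the existing condition that the event be judged at least possibly related to study drug. This also removes the mismatch between the lead-in's count and the two-subject entry.

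The cost is one phrase in an amendment. Table 4-1, blood volume, visits and sample size stay as they are. The downside is that suspension for an isolated related laboratory or QTcF value becomes somewhat more likely, which is what the stated limits call for. The retained attribution condition limits stops for unrelated out-of-range values.

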## **10. DATA ANALYSIS AND STATISTICAL CONSIDERATIONS**

### **10.1. General Considerations**

A comprehensive PK analysis plan (PKAP) and statistical analysis plan (SAP) that fully specifies the statistical methodology (including table, figure, and listing formats) for all aspects of the planned analyses will be developed by the Sponsor or Sponsor's designee. The PKAP and SAP will be developed as part of the pre-results clinical study report (CSR) and approved after the protocol is finalized. No database may be locked, or analyses completed until the SAP and PKAP have been approved. Additional unplanned analyses may be required after all planned analyses have been completed. Any unplanned analyses will be clearly identified in the CSR.

The SAP will provide a detailed description for the handling of missing data, patient eligibility criteria for the analysis, and statistical methodology for the data summary and analysis of safety. This protocol describes key analyses as currently contemplated. If differences occur between analyses described in the SAP and the current protocol, those found in the SAP will assume primacy.

All non-PK statistical reporting will be performed using the validated software SAS® for Windows version 9.4 or higher (SAS Institute, Inc., Cary, NC, USA), unless otherwise specified.

Individual subject data will be presented by subject in data listings. Data listings will include all data collected from the initial Screening visit up to the EOS for all subjects randomized. Both absolute values and change from baseline values for each subject will be given where applicable. Data listings will be sorted by treatment, SID, and time point. Screen failures will be included in a separate listing.

Continuous variables will be summarized using number of non-missing observations, mean, standard deviation (SD), median, minimum, and maximum; categorical variables will be summarized using the frequency count and the percentage of subjects in each category. In

addition to the descriptive summaries, pertinent data listings will be provided to facilitate case studies.

## **10.2. Determination of Sample Size**

A model-based approach was used to estimate power and sample size. Simulated subjects (n=1000) were randomized to a two-period crossover with two sequences (AB and BA) where Treatment A was GTX-104 and Treatment B was oral nimodipine. Incorporated sample collection times are outlined in the study design (Section 4.1). Day 3 simulated data were used for the AUC power analysis. The estimate for the within subject variance (on the log scale) came from a mixed effects model that included fixed effects for sequence, period, and treatment and a random effect for subject. Under the hypothesis that the true geometric mean ratio (GMR) is 1 for GTX-104 compared to oral nimodipine, a total of 49 subjects was estimated to provide power of 0.85 ( $C_{\max}$  on Day 1) and >0.99 ( $AUC_{\text{Day 3, 0-24hr}}$ ), respectively, to assess relative BA in a two-period, two-sequence crossover study.

A minimum of 60 subjects was therefore selected for enrollment to allow at least 50 subjects completing (allowing for some subject attrition). Additional subjects may be enrolled if subject withdrawal requires additional subjects to reach a total of 50 completers.

## **10.3. Analysis Populations**

Safety population: The Safety Population will consist of all subjects who receive at least 1 dose of study drug.

PK Population: The PK Population will consist of all subjects who receive at least 1 dose of study drug and have evaluable PK data.

Analysis Population: The Analysis Population will consist of those subjects in the PK population who are evaluable for both Treatment A (test) and Treatment B (reference).

## **10.4. Demographics and Baseline Characteristics**

Demographic and other baseline characteristics will be summarized by treatment group.

## **10.5. Pharmacokinetic Analyses**

A PKAP will be developed based on the latest version of the clinical protocol. No database may be locked, or analyses completed until the PKAP has been approved. The PKAP will provide a detailed description of the PK methodology, parameters, planned analyses, and tables, listings, and figures. This protocol describes key analyses as currently contemplated. If differences occur between analyses described in the PKAP and the current protocol, those found in the PKAP will assume primacy.

All PK parameters will be derived by noncompartmental analysis of the concentration-time data utilizing a validated installation of WinNonlin®, (Certara), version 6.4 or later. The models will be appropriate for plasma data from IV and oral administration. Actual sampling times will be used to calculate the PK parameters. The linear trapezoidal method will be used to integrate the concentration-time profile data.

### **10.5.1. Interim Pharmacokinetic Analysis**

An interim analysis may be conducted after ~20 subjects complete both periods to assess the within subject variability and the observed mean exposures. Individual nimodipine PK parameters will be calculated using noncompartmental analyses and will include  $C_{\max}$  on Day 1

for the first dose,  $AUC_{\text{Day 3, 0-24 hr}}$ ,  $C_{\text{max}}$  on Day 3, CL (for IV), and CL/F (for oral doses) at a minimum. The sample size may be increased by selecting an additional subjects for up to 100 to account for larger than anticipated variance(s) in  $AUC_{\text{Day 3, 0-24hr}}$  or  $C_{\text{max}}$  on Day 1 of first dose. If mean exposures are significantly dissimilar, the Treatment A dosing regimen may be modified. Any dose modifications would be described and justified in a protocol amendment.

